**Fig. 2 Fig2:**
[figure not shown]
Map of Chitungwiza

A local community hall or other forms of available and convenient gathering space will be identified in the respective communities as central data collection venues. The community leaders assisting in the recruitment processes will assist in identifying central venues convenient to participants recruited for the interventions and the study. Recruitment processes are detailed in the following section.

### Sample size

Past research has recommended sample sizes of 24 and 50 [28–31]. For this feasibility study, sample sizes for community leaders have been set at 25 in total, and for interventionists, at 25 per cluster; with the trial participants set at 75. The target is 50; however, a reach of 75 has been set, to allow for any challenges in recruitment and for possible attrition from the study.

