**Methods/design:**

This feasibility cluster randomized trial with embedded qualitative interviews will be conducted in two comparable neighborhoods in Zimbabwe. Community leaders from each neighborhood will identify 25 potential community lay bereavement supporters, each of whom will recruit 2–3 bereaved community members into the trial. The intervention will be randomly allocated to one community, and the second community will form a wait-list control (*n* ≥ 75 in each community cluster). Recruitment is estimated to take place over 3 weeks. Measures at T0 (baseline, i.e., week 0), T1 (midline, i.e., week 14 or 3 months post-baseline) and T2 (endline, i.e., week 27 or 3 months post-midline) will address mental health, social support, and levels of grief per individual. Qualitative data will describe lay supporters’ views of intervention training and delivery, and participants’ experience of bereavement support.

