### Feasibility questions and success criteria

We will seek to answer the following research questions: (1) will we be able to recruit at least 75% of the suggested sample size of interventionists and trial participants interventionists within 3 weeks? In order to meet proposed trial timelines, we suggest trial recruitment criteria of recruiting community leaders within 1 week; interventionists within 1 week and the trial participants within 1 week; giving a total recruitment period of 3 weeks. (2) Will we be able to retain at least 75% of both the trial participants and the interventionists in the total duration of the study? (3) Can we deliver the 9-cell bereavement intervention as intended? (4) Will the processes of a randomized cluster trial be possible? (5) Does process data suggest that the anticipated effect is likely?

There is a paucity of guidance on setting progression criteria for feasibility and pilot trials [25]. Therefore, we draw on the MRC guidance that such criteria should be judged in light of all study findings and used to refine study design. Our recruitment and retention criterion of 75% was set in light of published feasibility trial criteria and reflects the nature of our population (i.e., they are community-dwelling bereaved individuals without any known serious health conditions and so we anticipate high retention).

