#### Stage 2: Recruitment of potential interventionists by community leaders

The community leaders (CL) will be tasked to invite 25 people (i.e., potential interventionists) from their respective communities to attend a meeting. Inclusion criteria for potential interventionists will include individuals from the two selected communities of Chitungwiza which the CL serve; recruited by the community leaders; be aged at least 18 years of age; be able to either verbally consent or be able to consent in writing; be able to read and write; and expected to be able to deliver the lay community peer intervention. At the meeting, the potential interventionists will be provided with information about the study and asked to give informed consent, to participate in the study. Interventionists will complete a short questionnaire that will assess their socio-demographic background and bereavement history. The questionnaire is self-administered. The researchers will provide instruction to the interventionists and be available to assist with clarification of any questions where required. The third activity is a focus group discussion (FGD#1 as illustrated in Fig. 1) with the interventionists, to assess the feasibility of them identifying potential trial participants and inviting them to meet with the researchers, to learn more about the study.

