#### Stage 3: Recruitment of potential trial participants

The potential interventionists from each community will be tasked to identify 2 to 3 people according to the following criteria. Potential participants must be (a) at least 18 years old, (b) resident within their neighborhoods, (c) someone with whom they interact with on a daily basis, (d) whom they know to have been bereaved in the past 6 months, (e) would have the ability to either verbally consent or be able to consent in writing, (f) be able to read and write, and (g) be expected to attend and participate in the study. Potential participants who meet all of these criteria will be invited to a meeting where information regarding the study will be shared. Researchers will obtain consent from potential trial participants.

Following written informed consent, potential trial participants will be invited to participate in the study. Participating in the study includes completing questionnaires at baseline (T0, i.e., week 0), midline (T1, i.e., 3 months post-baseline or week 14), and endline (T2, i.e., 3 months post-midline or at week 27), with a subsample of the intervention cluster participants invited to qualitative focus group interviews to better understand participants’ views on study participation and intervention mechanisms of action. Focus group participants will be aged at least 18 years of age; be able to either verbally consent or be able to consent in writing; and be able to verbally share their experiences and thoughts regarding the study.

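### Read as per cluster, 75 participants is the most the recruitment route can deliver, so the allowance over the target of 50 is conditional and the two 75% recruitment criteria are chained

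*Protocol article*

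**What the plan says.** The Sample size section fixes the numbers "for interventionists, at 25 per cluster; with the trial participants set at 75". It then names 50 as the target and adds that "a reach of 75 has been set, to allow for any challenges in recruitment and for possible attrition from the study". It does not say whether the participant figures are per cluster or in total. The Abstract (Methods/design) does: at least 75 in each community cluster. Stage 4 (baseline data collection) gives a third figure, 25 trial participants per community.

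The route to those participants is described in three places. Under Stage 2, community leaders "will be tasked to invite 25 people (i.e., potential interventionists) from their respective communities". Under Stage 3, those supporters "will be tasked to identify 2 to 3 people according to the following criteria". The Abstract describes the same step as supporters "each of whom will recruit 2–3 bereaved community members into the trial". The article describes no other route, no replacement of supporters who decline, and no naming of extra people to cover refusals.

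The first feasibility question asks: "will we be able to recruit at least 75% of the suggested sample size of interventionists and trial participants". The second sets 75% for retention of both groups.

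**The concern.** The figure of 75 is meant to absorb recruitment problems and attrition. If it is also the most that the supporters can name, it is reached only when no recruitment problem occurs, and the size of the allowance depends on how many people each supporter happens to name.

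The second issue is how the criteria read. Participants come only through supporters, so a shortfall of supporters carries over into the participant count. Two criteria presented as separate tests would then partly measure the same thing. Recruitment feasibility is objective (i), and the criteria feed the judgement on whether a full trial is warranted, so it matters whether a low participant count reflects few supporters, few names per supporter, or few nominees agreeing.

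**Working it through.** **Inputs.** Supporters per cluster: 25 (Sample size; Stage 2). People named per supporter: 2 to 3 (Stage 3; Abstract). Target 50 and reach 75 (Sample size), taken per cluster as in the Abstract. Recruitment and retention criteria: 75% each (Feasibility questions and success criteria).

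**Step 1: reproduce the plan's figures.** Yield = supporters × names per supporter.
- Two each: 25 × 2 = 50, the target.
- Three each: 25 × 3 = 75, the reach.

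The target is the bottom of the range and the reach is the top. Reaching 75 needs all 25 invitees to join, each to name three different people, and all 75 to be eligible and consent.

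**Step 2: the allowance over 50.**
- Three each: 75 − 50 = 25 places, a tolerable combined loss of 25/75 = 33%.
- Mean of 2.5 each (assumption): 62.5 − 50 = 12.5 places, a tolerable loss of 12.5/62.5 = 20%.
- Two each: 50 − 50 = 0.

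**Step 3: the chained criteria.**
- Supporter pass: 0.75 × 25 = 18.75, so 19.
- Names available from 19 supporters: 19 × 2 = 38 to 19 × 3 = 57.
- Participant pass with 75 as denominator: 0.75 × 75 = 56.25, so 57. Margin: 57 − 57 = 0.
- Participant pass with 50 as denominator: 0.75 × 50 = 37.5, so 38. This is met even at two names each if nobody is lost.
- Pooled over two clusters: 0.75 × 50 supporters = 37.5, so 38; 38 × 3 = 114 names, against 0.75 × 150 = 112.5, so 113. The margin is one person.

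**Step 4: after attrition.** 57 recruits × 0.75 retained = 42.75, about 43. Keeping 50 of 57 would need 50/57 = 88% retention.

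**Step 5: how likely each outcome is.** The documents give no uptake rate and no split between two and three names, so both are assumptions here. Each supporter names three with the probability shown, otherwise two, and each nominee joins independently at the stated uptake.

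| Supporters | Naming three | Uptake | Result for one cluster |
|---|---|---|---|
| 25 | half | 90% | P(≥50) = 0.98; P(≥57) = 0.48 |
| 25 | half | 80% | P(≥50) = 0.56; P(≥57) = 0.04 |
| 25 | half | 95% | P(≥57) = 0.84 |
| 19 | all | 90% | P(57 of 57) = 0.9^57 = 0.0025 |
| 19 | all | 95% | P(57 of 57) = 0.95^57 = 0.054 |
| 19 | half | 90% | P(≥38) = 0.97; P(≥57) ≈ 0 |
| 19 | half | 80% | P(≥38) = 0.57 |

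The target of 50 is likely to be reached with all 25 supporters and 90% uptake. At the supporter pass mark, the participant verdict turns almost entirely on whether 50 or 75 is the denominator.

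**The case against.** A reader might infer that the allowance for recruitment problems does not exist at all. The documents do not support that. The Sample size section defines the allowance as 75 over a target of 50, not as slack above 75. Those 25 places exist if supporters name three each, and even the capped figure of 57 exceeds 50.

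A reader might also infer that a bare supporter pass makes the participant stage fail. It does not by definition: 57 still meets the threshold when 75 is the denominator. The success criteria refer only to the suggested sample size, which could equally mean 50, with a threshold of 38. The problem is sharpest only when the supporter stage just passes.

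Nor do the documents support saying that the trial would record a shortfall as unwillingness to take part. The Data analysis section reports recruitment for supporters and participants separately, the first focus group examines whether supporters can identify participants, and the criteria are to be judged in the light of all findings. A supporter shortfall would be visible. What is left is that the participant criterion itself does not separate the causes.

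The strongest objection concerns the unit. The per-cluster reading comes from the Abstract. Stage 4's 25 per community makes 50 in total, which fits the target of 50 as a two-cluster total. If 50 and 75 are both totals, 50 supporters could name 100 to 150 people and the capacity problem disappears. The Abstract is explicit, however, and 25 × 3 reproduces 75 exactly at cluster level, so the per-cluster reading is the better supported one for 75. The conflict among the three places stands either way.

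**Conclusion.** The point holds in a limited form. On the Abstract's per-cluster reading, the stated minimum of 75 equals the maximum of the described route. The allowance over 50 ranges from 25 places down to none within the two-to-three instruction. At the smallest supporter pass, a cluster can name 38 to 57 people. That leaves no margin on the participant criterion if 75 is the denominator (one person if pooled over clusters). A cluster that passes recruitment at 57 and retention at 75% ends with about 43, short of the target.

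These capacity figures rest on the protocol's own numbers and on the per-cluster reading; only the probabilities depend on assumed uptake and naming. The consequence is a stated size that the described route delivers only under ideal conditions, and a progression criterion whose reading depends on an unstated denominator. It is worth correcting, but it does not show that the target of 50 is out of reach.

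**What to change.** 1. In the Abstract and Sample size section, replace the minimum of 75 per cluster with the capacity of the route: 50 to 75 per cluster with all 25 supporters, and 38 to 57 at the supporter pass mark of 19.
2. State the denominator of the participant criterion. Either use the target of 50 (threshold 38 per cluster), or define the criterion relative to the supporters actually recruited: people enrolled per supporter, and the proportion of those identified who enrol. The second form keeps a supporter shortfall from being counted again as a participant shortfall.
3. Reconcile the per-cluster and total figures in the Abstract, Sample size and Stage 4.

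Raising the number each supporter names is optional. With 25 supporters, three to four names each would give 75 to 100 nominees, so it would need a cap of 75 enrolled per cluster. Inviting more supporters instead could exceed the 25 to be trained under Stages 5 and 6.

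The cost is a few changed sentences and a less favourable stated sample size. Items 1 to 3 add no participants and no data collection.

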### Recruitment

The recruitment process follows three stages.

#### Stage 1: Recruitment of community leaders

The recruitment process will begin with study engagement using existing relationships that Island Hospice and Healthcare (IHH) has with community leaders (CL) from the selected two communities in Chitungwiza. The rationale, goals, and intended procedures of the study will be explained, community leader permission sought to undertake the research, and support from the community leaders (CL) requested to deliver the study. This is an essential step in conducting community-based research in this context.

#### Stage 2: Recruitment of potential interventionists by community leaders

The community leaders (CL) will be tasked to invite 25 people (i.e., potential interventionists) from their respective communities to attend a meeting. Inclusion criteria for potential interventionists will include individuals from the two selected communities of Chitungwiza which the CL serve; recruited by the community leaders; be aged at least 18 years of age; be able to either verbally consent or be able to consent in writing; be able to read and write; and expected to be able to deliver the lay community peer intervention. At the meeting, the potential interventionists will be provided with information about the study and asked to give informed consent, to participate in the study. Interventionists will complete a short questionnaire that will assess their socio-demographic background and bereavement history. The questionnaire is self-administered. The researchers will provide instruction to the interventionists and be available to assist with clarification of any questions where required. The third activity is a focus group discussion (FGD#1 as illustrated in Fig. 1) with the interventionists, to assess the feasibility of them identifying potential trial participants and inviting them to meet with the researchers, to learn more about the study.

#### Stage 3: Recruitment of potential trial participants

The potential interventionists from each community will be tasked to identify 2 to 3 people according to the following criteria. Potential participants must be (a) at least 18 years old, (b) resident within their neighborhoods, (c) someone with whom they interact with on a daily basis, (d) whom they know to have been bereaved in the past 6 months, (e) would have the ability to either verbally consent or be able to consent in writing, (f) be able to read and write, and (g) be expected to attend and participate in the study. Potential participants who meet all of these criteria will be invited to a meeting where information regarding the study will be shared. Researchers will obtain consent from potential trial participants.

Following written informed consent, potential trial participants will be invited to participate in the study. Participating in the study includes completing questionnaires at baseline (T0, i.e., week 0), midline (T1, i.e., 3 months post-baseline or week 14), and endline (T2, i.e., 3 months post-midline or at week 27), with a subsample of the intervention cluster participants invited to qualitative focus group interviews to better understand participants’ views on study participation and intervention mechanisms of action. Focus group participants will be aged at least 18 years of age; be able to either verbally consent or be able to consent in writing; and be able to verbally share their experiences and thoughts regarding the study.

#### Retention of interventionists and trial participants

Registration forms will include full names and contact details of both interventionists and trial participants. Contact details will be used to notify both interventionists and trial participants, of the planned data collection dates respectively. For example, mobile phone messages will be sent to all both the interventionists and the trial participants, requesting and reminding them of the dates for baseline, midline, and endline data collection.

#### Stage 4: Baseline data collection from trial participants

Once recruited into the study, the trial participants (*n* = 25 per community) will complete self-report questionnaires, both demographic and validated outcome measures. Data collection will be on different days for each community, but within a space of a week. Questionnaires will be self-administered, with assistance from researchers where needed. Trained surveyors will go through some sample questions with the respondents in order to familiarize them with the questionnaire format. The surveyors will be present to assist respondents who may require further assistance beyond initial instructions. Completing the questionnaires is estimated to take less than an hour.

The questionnaires used were selected as they are in line with the intended intervention outcomes, have been successfully tested to be culturally specific adaptation, have been used by other researchers in Africa and or other low- and middle-income countries, and their ease of understanding and therefore administration.

These are the Shona Symptom Questionnaire (SSQ, measure mental health), the Modified Social Support Survey (MSSS, measures social support), and the Texas Revised Inventory of Grief (TRIG, measures levels of grief). The SSQ was developed in Zimbabwe. It incorporates 14 questions, 7 of which are etic (global concept) and 7 are emic (culturally specific). The MSSS has 20 questions based on 4 subscales of emotional/informational, tangible, affectionate, and positive social interactions [32]. The TRIG is a 13-item, self-report measure of current feelings related to the loss [33]. As an illustration of their successful adaptability in different and varied cultural settings and languages, the MSSS and the TRIG have both been successfully used in both low- and high-income countries including Brazil—Portuguese language [34]; the USA [35]; in French Canada [36]; in New Mexico [37]; Norway [38]; and Spain [39].

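### The number of trial participants is stated in three ways that do not agree, so the 75% recruitment criterion has no fixed denominator

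*Protocol article*

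**What the plan says.** Four places in the protocol article bear on the number of trial participants.

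- **Abstract, Methods/design.** The planned number is at least "75 in each community cluster". The abstract also has 25 lay supporters identified in each neighborhood, "each of whom will recruit 2–3 bereaved community members into the trial".
- **Sample size.** Interventionists are given per cluster and community leaders in total. Trial participants get a number without a unit: "with the trial participants set at 75. The target is 50; however, a reach of 75 has been set". The larger figure is there to absorb recruitment difficulty and attrition.
- **Stage 3.** On the recruitment step: "The potential interventionists from each community will be tasked to identify 2 to 3 people".
- **Stage 4.** On baseline data collection from trial participants: "25 per community) will complete self-report questionnaires, both demographic and validated outcome measures".

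Two places use the number. Feasibility question 1 asks "will we be able to recruit at least 75% of the suggested sample size" of interventionists and trial participants within 3 weeks. The Data analysis section reports recruitment as a share of the target sample and measures success by the criteria set beforehand. Neither place attaches a participant count to its term.

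**The concern.** The abstract and Stage 4 state the same quantity in the same unit and differ threefold (75 against 25 per community). The Sample size section does not decide between them. Read as a trial-wide total, its target of 50 matches Stage 4 (2 × 25). Read per cluster, its 75 matches the abstract.

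Recruitment is part of objective (i) and is the first feasibility question. A percentage criterion is set in advance only if its denominator is. As written, someone appraising the results could choose the denominator after seeing how many people were recruited, and the same recruitment could be reported as meeting the criterion or missing it. That weakens the article's stated purpose of transparent analysis with less reporting bias.

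The problem concerns trial participants only. The interventionist denominator, 25 per cluster, is clear.

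**Working it through.** There is no power calculation to reproduce: the Sample size section rests on sizes recommended for such studies. The check is therefore whether the stated numbers follow from the recruitment plan, and what each implies for the 75% criterion.

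**Inputs**
- Clusters: 2 (abstract; Setting).
- Interventionists per cluster: 25 (Sample size).
- Participants per interventionist: 2 to 3 (abstract; Stage 3).
- Criterion: at least 75% of the sample size (Feasibility questions and success criteria).

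**Step 1. Planned yield per cluster = interventionists × participants each**
- Lower: 25 × 2 = 50 per cluster, 100 in total.
- Upper: 25 × 3 = 75 per cluster, 150 in total.

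The 50 and the 75 in the Sample size section are both reproduced if read per cluster. The 25 per community in Stage 4 is not, since it is half the lower yield. The abstract's minimum of 75 equals the upper yield, so the plan reaches it only if the interventionists average three enrolled participants each.

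**Step 2. Pass mark in total participants = 0.75 × N, rounded up**

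| Denominator | N in total | 0.75 × N | Pass mark |
|---|---|---|---|
| 75 per cluster | 150 | 112.5 | 113 |
| 50 per cluster | 100 | 75 | 75 |
| 75 in total | 75 | 56.25 | 57 |
| 50 in total (25 per community) | 50 | 37.5 | 38 |

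**Step 3. Where the verdict depends on the denominator**
- Across all four readings, any total from 38 to 112 passes under at least one and fails under at least one other.
- 60 recruited: 60/50 = 120% and 60/75 = 80% pass; 60/100 = 60% and 60/150 = 40% fail.
- 100 recruited: 100/100 = 100% passes; 100/150 = 67% fails.

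**Step 4. Stage 4 set aside, and 50 and 75 read per cluster**

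The choice is then between N = 100 and N = 150, with pass marks of 75 and 113 (a ratio of about 1.5). Totals from 75 to 112 still pass on one and fail on the other. Correcting Stage 4 alone does not settle the criterion.

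**The case against.** The strongest reply is that the denominator is less open than four readings suggest. The criterion's wording points to the Sample size section, which calls 50 the target, and the Data analysis section also speaks of a target. Stage 4 describes who fills in questionnaires and sets no target. In "for interventionists, at 25 per cluster; with the trial participants set at 75" the unit given for interventionists can be carried forward to participants. On that reading the abstract, the Sample size section and Stage 3 largely agree, and Stage 4 is the outlier, perhaps a carry-over of the interventionist count. Much of this stands: it is the most coherent reading, and 57 is the weakest of the four marks because the abstract contradicts 75 as a trial-wide total. But it is inference. A total of 50 is not excluded, since it matches Stage 4, and the choice between 50 and 75 per cluster stays open.

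A second reply also stands. The article says its criteria are to be weighed with everything the study finds and used to refine the design. No stop/go decision hangs on the 75%, and no test or power claim depends on the number. That limits the harm but does not supply a denominator.

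Two stronger readings are tempting and are not supported. A reader might infer that 75 per cluster can never be exceeded. The plan tasks each interventionist with 2 to 3 people but states no cap, so 75 is only the top of the planned yield. A reader might also translate the spread in sample size into a loss of precision for the comparison between communities. With one cluster per arm, the intervention effect cannot be separated from the difference between the two communities. A formula for independent samples therefore does not give that precision, and it has no bearing on the recruitment criterion.

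**Conclusion.** The inconsistency is real and lies within the article itself, so an unseen full protocol or analysis plan would not remove it. The participant number is at least 75 per cluster, 75 with a target of 50 and no unit, or 25 per community, and these cannot all hold. As a result the recruitment criterion has no fixed pass mark: it runs from 38 to 113 in total across all readings, and is 75 or 113 on the most coherent one.

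The narrower range assumes that 50 and 75 are per cluster and that Stage 4 is an error. Both are plausible from the recruitment plan, but neither is stated. It would go too far to say that the feasibility decision as a whole turns on this, because the criterion is one input to an overall judgement.

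**What to change.** Before results are appraised:

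1. Reconcile the abstract, the Sample size section and Stage 4 to one participant target, stated per cluster and in total. If a larger recruitment reach is kept, label it as a reach and give it the same unit.
2. Name that target as the denominator in feasibility question 1 and in the recruitment paragraph of Data analysis, using the same term in both.
3. Give the pass mark as a count, and say whether it applies to the total or to each cluster. This matters slightly because of rounding: with 50 per cluster the mark is 75 in total, but 38 in each cluster (0.75 × 50 = 37.5), which makes 76.

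A target of 50 per cluster (100 in total, pass mark 75) with a reach of 75 per cluster fits the recruitment plan best. The sponsor must confirm that this was intended, because it would change the abstract's minimum of 75 per cluster. The cost is wording only; no design, data collection or analysis method changes.
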